## Abstract

**Background:**

Upper limb dysfunction after stroke is one of the common problems. Tai Chi Yunshou exercise and seated Tai Chi exercise have been confirmed that it is beneficial on upper limb function for stroke patients. Seated Tai Chi Yunshou exercise easier and suitable for stroke patients who are unable to stand. The purpose of this experiment is to explore the effects of seated Tai Chi Yunshou exercise on the upper limb function for stroke patients.

**Methods:**

84 stroke patients with upper limb dysfunction were randomly divided into two groups. The experimental group and the control group consist of 42 patients each. The experimental group will receive seated Tai Chi Yunshou training combined with conventional treatment, while the control group only will receive conventional training. Each training session will be implemented once a day and five times per week in a duration of 4 weeks. Primary and secondary outcomes will be measured at baseline and 4-weeks, 8-week follow-up after randomization. Fugl-Meyer Upper Extremity Assessment (FMA-UE) will be the primary outcome and Modified Trunk Impairment Scale (mTIS),the Wolf Motor Function Test (WMFT), Functional near-infrared spectroscopy (fNIRS), Barthel Index(BI) will be the secondary outcome. Functional near-infrared spectroscopy(fNIRS) will be used to explore the therapeutic mechanism.

**Discussion:**

According to previous studies, Tai Chi Yunshou exercise and tailored seated Tai Chi are effective treatment for stroke patients. In this study, we will conduct a seated Tai Chi Yunshou exercise for patients with stroke. We believe that this study may prove the effectiveness of seated Tai Chi Yunshou exercise on upper limb function among stroke patients.

**Trial registration:**

ClinicalTrials.gov ChiCTR2400085317

## Introduction

Upper limb dysfunction is a common and particularly challenging impairment experienced by stroke patients [1]. It is caused by factors such as reduced motor function, sensory loss, ataxia, spasticity, and pain, which hinder the independent performance of functional activities that require upper limb involvement, such as eating, dressing, and washing [2]. About 80% of people with acute stroke have upper limb motor impairment, and of those with reduced arm function early after stroke [3]. There are various methods for upper limb rehabilitation, including muscle strength training, sensory training, motor control training, task-oriented training, constraint-induced movement therapy, and robot-assisted upper limb training. These rehabilitation exercises often emphasize repetitive training of specific body parts, while coordinated training between different limbs is relatively rare, and the interaction between different body parts is seldom prioritized. Meanwhile, the integration of cognitive and motor functions receives little attention [4]. However, the trunk and upper limbs often work in synergy during activities, and the underlying brain mechanisms require further study.

Brain functional specialization emphasizes hemispheric processing, enabling the expanded human brain to minimize inter-hemispheric connectivity and allocate specific processing functions, with relatively less cognitive involvement [5,6]. Improvements in inter-hemispheric functional specialization may enhance the efficiency of cognitive processing [7]. In real-life functional activities, the involvement of different limb movements and cognition often requires coordination between the two hemispheres. Tai Chi is a holistic mind-body activity that helps practitioners focus their attention, regulate breathing, and improve motor function [8]. It emphasizes coordination between different limbs, the interaction between movement and cognition, and the coordination between movement and breathing, focusing on the connection between the two cerebral hemispheres. Long-term Tai Chi practice can optimize functional connectivity in brain regions that play a crucial role in cognitive-motor integration [9]. Performing the Tai Chi Yunshou movement leads to higher activation of the motor cortex and prefrontal cortex, which, in the long term, results in enhanced or remodeled functional connectivity in brain regions [6,10].

In the present study, we situate our investigation within established neurorehabilitation frameworks—including Dynamic Systems Theory (DST), Task-Oriented Training (TOT), and the International Classification of Functioning, Disability and Health (ICF)—to theoretically ground the application of seated Tai Chi Yunshou for post-stroke recovery. Guided by DST, we conceptualize Yunshou not merely as exercise but as a task-specific constraint that promotes self-organization of the neuro-musculo-skeletal system toward more functional and stable coordination patterns, facilitated by its rhythmic, bilateral, and multi-joint nature [11]. Its movement patterns, such as pushing, pulling, and weight-shifting, mirror components of activities of daily living, aligning with TOT principles that emphasize functional, goal-directed practice to promote neuroplasticity [12]. Potential outcomes are framed within the ICF model, spanning improved interhemispheric connectivity (Body Function & Structure), enhanced bimanual coordination and upper limb function (Activity), and increased engagement in daily life (Participation). Current research has demonstrated the benefits of seated Tai Chi and Tai Chi Yunshou for upper limb function in stroke patients [11–13]. Tai Chi is an exercise centered around the waist, and compared to regular Tai Chi, seated Tai Chi emphasizes the linkage between the trunk and upper limbs [14]. Tai Chi is a complex exercise that is difficult to learn in a short period. The Yunshou movement in Tai Chi is a fundamental form that well reflects the essence of Tai Chi [15–17]. However, many subacute stroke patients are unable to perform Tai Chi Yunshou training due to poor standing balance. Therefore, this study aims to investigate the effects of seated Tai Chi Yunshou training on upper limb function and brain functional mechanisms in subacute stroke patients.

## Methods

### Study design

A single-center, parallel, randomized controlled trial was designed to explore the effects of seated Tai Chi Yunshou on upper limb function in patients with subacute stroke. This trial design was approved by the Ethics Committee of Shuguang Hospital Affiliated to Shanghai University of Traditional Chinese Medicine (Approval No. 2023-1414-181-01) and registered on the Chinese Clinical Trial Platform (Registration No. ChiCTR2400085317).

### Participants

All subjects will be recruited from the rehabilitation department of Shuguang Hospital Affiliated to Shanghai University of Traditional Chinese Medicine, with recruitment taking place from September 1, 2025, to September 30, 2026. Subjects will be recruited based on the following criteria:

Doctors will screen patients admitted to the hospital and referred those who might meet the inclusion criteria for the study to the research leader.The researchers will introduce the concept of the trial to potential patients and inquire whether they will be willing to participate voluntarily.Subjects will undergo an assessment process.Subjects will sign an informed consent form before the start of the trial.

#### Inclusion criteria.

In accordance with the diagnostic criteria of the ‘Chinese guidelines for diagnosis and treatment of AIS’ (2018 version)and confirmed by CT or MRI examination.

First episode of stroke

Onset time between 2 weeks to 6 months

Seated balance at Level 1 or above

Unilateral limb impairment

Able to tolerate 30 minutes of seated Tai Chi Yunshou exercise and signed informed consent.

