### Sample size

This trial aims to assess the impact of Tai Chi on upper limb function in post-stroke patients. Using G-power V.3.1.9.2 software for sample size calculation, the Fugl-Meyer Assessment Upper Extremity (FMA-UE) scale was selected as the primary outcome measure. Based on data from a previously published study [18], the mean FMA-UE scores post-intervention were 60.50 ± 2.19 for the Tai Chi group and 59.14 ± 1.77 for the control group. To detect the targeted effect size of 0.6830377 with a type 1 error rate of 5% (α = 0.05) and 80% statistical power (β = 0.20), a sample size of 64 participants is deemed sufficient. Accounting for a potential dropout rate of 20%, a total of 84 participants will be enrolled, with 42 participants assigned to each group.

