### Randomization and blinding

Eligible subjects who fulfill the inclusion criteria and provide signed informed consent will undergo randomization, allocated in a 1:1 ratio to either the control or intervention groups. The randomization process will be computer-generated using a block randomization design with a fixed block size of 4, implemented by independent statistical experts blinded to study details. The random allocation sequence will be produced using SPSS software to ensure randomness and reproducibility. To maintain the integrity of the randomization, therapists not directly involved in recruitment, assessment, or intervention will securely place each allocated number into an opaque envelope. Following patient screening, the recruitment physician will liaise with a designated coordinator who will then dispatch the necessary documentation to eligible subjects, informing them of their group assignment. This rigorous randomization procedure aims to minimize bias and ensure the validity of the study results.

Owing to the inherent characteristics of the intervention, it is not feasible to blind the subjects and therapists directly involved in the intervention process. However, throughout the duration of the study, the therapist conducting assessments, the researcher tasked with data collection, and the statistician analyzing the data will remain blinded to group allocations. This blinding protocol will be maintained until the completion of statistical analyses to minimize potential bias. Once the statistical analyses are concluded, the blinding will be lifted.

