### Statistical analysis

Statistical analyses were conducted utilizing IBM SPSS 26.0 software. In terms of descriptive statistics, qualitative indicators were represented by percentages, while quantitative indicators were summarized using means and standard deviations. For quantitative data, an independent samples t-test was applied when the data followed a normal distribution. In cases where normality assumptions were not met, the non-parametric Wilcoxon rank sum test was employed. Qualitative data were analyzed using the chi-square test, and rank data were examined with the Wilcoxon rank sum test. For datasets containing multiple observation time points, a repeated measures ANOVA was utilized to account for the longitudinal nature of the data. Statistical significance was determined at a P-value less than 0.05. For longitudinal data violating normality/sphericity, the non-parametric Friedman test replaced repeated measures ANOVA.

Given the limited sample size (N = 84) in this study, Multiple Imputation (MI) was employed to address missing data. This method generates multiple complete datasets and pools analysis results, thereby mitigating the bias associated with single imputation in small-sample studies. All imputation procedures were conducted using the MICE package in R, with five parallel imputations performed to ensure stability.

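### Entry runs from 2 weeks to 6 months after stroke, but the FMA-UE comparison described does not use time since onset, which costs power if recovery differs across that window

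*Protocol article*

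**What the plan says.** The Inclusion criteria set the entry window as "Onset time between 2 weeks to 6 months", roughly 2 to 26 weeks.

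Randomization and blinding describes patients "allocated in a 1:1 ratio to either the control or intervention groups" by a "block randomization design with a fixed block size of 4". It names no stratification factor.

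Statistical analysis says that for quantitative data "an independent samples t-test was applied when the data followed a normal distribution", with a Wilcoxon rank sum test otherwise. For several time points, "a repeated measures ANOVA was utilized to account for the longitudinal nature of the data", with a Friedman test as the fallback. No covariate is named for any of these.

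Sample size takes its planning values from an earlier published study: "60.50 ± 2.19 for the Tai Chi group and 59.14 ± 1.77 for the control group". From these it derives an effect size of 0.6830377, 64 participants before dropout and 84 enrolled, 42 per arm.

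**The concern.** Time since onset is a plausible predictor of how much a patient's FMA-UE changes over the 4 weeks of treatment, whatever the arm, and the entry window is wide: the longest permitted time is about 26 / 2 = 13 times the shortest. If early and late patients recover at different rates, an analysis that ignores onset counts that difference as noise. With a target of only 1.36 points, added noise matters.

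This is not the same issue as starting level. A repeated measures ANOVA that includes the baseline visit takes account of where a patient starts on FMA-UE. It does not take account of two patients with the same starting score being expected to gain different amounts because one is 3 weeks and the other 5 months after stroke.

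At stake is the chance of detecting the planned effect. The trial was sized for 80% power, so even a moderate increase in error variance can take it below that.

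**Working it through.** **Inputs from the protocol.** Means 60.50 and 59.14, SDs 2.19 and 1.77, α = 0.05 (sidedness not stated; two-sided is taken here), 64 participants before dropout (32 per arm), 84 enrolled (42 per arm).

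**Reproducing the plan's figures.**
- Difference: 60.50 − 59.14 = 1.36 points.
- Pooled SD: √((2.19² + 1.77²)/2) = 1.991.
- Effect size: 1.36 / 1.991 = 0.683, as stated.
- Two-sided t-test power at this effect size: 76.7% with 32 per arm and 87.1% with 42 per arm. The stated 64 does not give 80% two-sided (35 per arm, 70 in total, would). That is a separate matter, but it explains why the 32-per-arm baseline below is 77%.

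**Assumptions needed.** The documents give neither a recovery rate by time since onset nor the expected spread of onset times. Two readings of the SD of 1.99 bracket the question. Power is from the noncentral t distribution.

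*Reading A: 1.99 is the total SD, and onset explains a share R² of the variance.* Adjustment reduces the SD to 1.991 × √(1 − R²), so the effect size becomes 0.683 / √(1 − R²).

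| R² | Adjusted SD | Effect size | Power, 32 per arm | Power, 42 per arm |
|---|---|---|---|---|
| 0 (unadjusted) | 1.991 | 0.683 | 77% | 87% |
| 10% | 1.889 | 0.720 | 81% | 90% |
| 20% | 1.781 | 0.764 | 85% | 93% |

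*Reading B: 1.99 is the residual SD among patients of similar onset time.* Suppose half the patients are early and gain g points more than the late half. The total SD is then √(1.991² + (g/2)²). The unadjusted test works against that SD, the adjusted one against 1.991.

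| g (points) | Total SD | Unadjusted effect size | Unadjusted power, 42 per arm | Adjusted power, 42 per arm |
|---|---|---|---|---|
| 2 | √(3.964 + 1) = 2.228 | 0.610 | 79% | 87% |
| 4 | √(3.964 + 4) = 2.822 | 0.482 | 59% | 87% |

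**Validity.** A simulation with 42 per arm, onset uniform on 2 to 26 weeks, residual SD 1.991 and 6,000 runs per scenario gave an unadjusted type I error of 4.7% to 5.3%. The assumed difference in gain between the two ends of the window ran from 5 to 20 points. The test holds its level.

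**Chance imbalance.** With 42 of 84 patients early and 42 per arm, the hypergeometric probability that the arms differ by at least 6/42 (14 percentage points) in the share of early patients is 0.275, and by at least 8/42 (19 points) 0.126. The chance that the resulting shift reaches 1.36 points in either direction depends on the assumed gap: 0.1% at 4 points, 1.6% at 5, 4.9% at 6 and 12.6% at 8.

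**The case against.** A reader might infer something stronger: that chance imbalance in onset time can rival the 1.36-point target, or create an effect that is not there. The documents do not support this. They state no gap between early and late patients, and with an assumed gap of 4 points a shift of 1.36 is a 0.1% event; it reaches 12.6% only at 8 points. Such a gap also fits poorly with the planning figures: between two equal halves, 4 to 8 points means an SD of 2 to 4 from onset alone, as large as or larger than the whole planning SD. If 1.99 is the total SD, even 50% of variance explained by onset leaves about a 0.001% chance of a 1.36-point shift. Nor is chance imbalance under randomisation a bias, since the ordinary test already allows for it. This objection stands in full.

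It can also be said that unstratified blocks are a valid design for 84 patients at one site, and that a condensed article may leave covariates to an analysis plan not shown. The first is right: stratification is a preference. The second stands in part. Lack of adjustment can be asserted only of the article's text. But the article does not leave the tests open. It names them, and the t-test and the standard Wilcoxon and Friedman tests take no covariate.

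On the other side, the planning SD comes from an earlier study, and nothing in the protocol shows that its patients covered the same onset window. If they did not, the SD in this trial may be larger than 1.99, which makes adjustment more useful.

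**Conclusion.** The point holds as one about precision. A wide onset window, no named stratification factor and unadjusted tests leave a plausible prognostic variable in the error term, although it must be known for every patient from the eligibility check. The described analysis is valid but may be less powerful than it need be.

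The size is conditional. Under reading A the gain from adjustment is modest: about 3 to 6 percentage points of power with 42 per arm and 4 to 9 with 32 per arm. Under reading B it is larger: about 8 points for a 2-point gap, which already puts the unadjusted analysis just under 80% with all 84 patients, and about 28 points for a 4-point gap. The assumed 10–20% of variance, the 2–4 point gap and the half-and-half split are not in the documents. If recovery does not vary with onset, nothing is gained and one degree of freedom is spent.

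**What to change.** State in Statistical analysis that the group comparison of FMA-UE at week 4 and at follow-up is adjusted for time since onset and baseline FMA-UE. Use ANCOVA at each time point or a mixed model over both, in place of the unadjusted t-test or Wilcoxon test. Fix how onset time enters the model (for example as a continuous term in weeks) before any unblinded data are seen.

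The cost is small. Both covariates are already collected, a continuous onset term uses one degree of freedom, and no patients or visits are added. As a protocol change it goes through the Steering Committee and IRB route in the Quality control section.

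Stratifying the allocation of patients still to be randomised by onset is optional. Recruitment is under way, so it would mean changing the allocation list midway under the same approvals, and the covariate recovers the precision without it.

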#### Exclusion criteria.

MMSE score of 23 or less

Unable to tolerate 30 minutes of sitting Tai Chi Yunshou exercise

Presence of other serious illnesses, such as heart disease, kidney failure, tumors, etc.

Patients will be randomly assigned to the experimental group or the control group based on a computer-generated random sequence. Before the trial, patients will receive a sealed, opaque envelope determining their group assignment. A dedicated person will be responsible for data collection and group assignment. Assessments will be conducted by physical therapists who will be unaware of the experimental grouping and treatment plan. Participants in the trial will not be allowed to exchange information.

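### One person is given both group assignment and data collection although data collection is said to be blinded; separately, fixed blocks of 4 let informed staff infer some upcoming allocations

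*Protocol article*

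**What the plan says.** The article describes allocation twice.

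- **Exclusion criteria, closing paragraph:** "A dedicated person will be responsible for data collection and group assignment". The next sentence gives the assessments to physical therapists who do not know the grouping.
- **Randomization and blinding:** "the researcher tasked with data collection, and the statistician analyzing the data will remain blinded to group allocations", along with the assessing therapist. On duration: "This blinding protocol will be maintained until the completion of statistical analyses to minimize potential bias". This section divides the allocation work among several people. Independent statisticians generate the sequence, "therapists not directly involved in recruitment, assessment, or intervention will securely place each allocated number into an opaque envelope", and a designated coordinator, contacted by the recruiting physician, tells patients their group.

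The second section also sets the form of the list. Patients are "allocated in a 1:1 ratio to either the control or intervention groups", using "a block randomization design with a fixed block size of 4". It accepts that "it is not feasible to blind the subjects and therapists directly involved in the intervention process".

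Study design describes a single-centre trial, and Participants names one hospital's rehabilitation department as the only source of patients. Quality control, however, refers to four participating centres. Trial status says recruitment is still open and may end in September 2026.

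**The concern.** There are two separate issues.

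**Roles.** Whoever assigns groups knows the groups. If that person also collects the data, the blinding of data collection claimed elsewhere is not true. A reader cannot tell which account will be followed, or who knows the allocation. The Rejection criteria make this more than a matter of wording. They allow participants to be removed for protocol breaches or deterioration, and data sets to be discarded after equipment faults. These are judgements, the article does not say they are made blind, and a collector who knows the allocation would be placed to influence them. Such a person could also disclose allocation to the blinded assessors.

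**Predictability.** With one published block size, past allocations carry information about the next. Referring doctors have some discretion: eligibility includes tolerating 30 minutes of exercise, and the serious-illness exclusion is open-ended. Someone who could infer the next allocation could change whom they refer, or when. That would be selection bias.

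**Working it through.** **Roles.** No arithmetic applies. The Exclusion criteria paragraph says one person does assignment and data collection. Randomization and blinding says the data-collection researcher does not know allocation until the analyses are complete. Both are current text, and they are incompatible for the same person. Outcome scoring is not affected by this conflict: the Exclusion criteria paragraph, Randomization and blinding, and Measures all give it to separate blinded assessors. Data management adds two blinded data managers for dual entry.

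**Predictability: inputs.** Block size 4 and ratio 1:1 (Randomization and blinding); 84 patients (Sample size). This gives 84/4 = 21 blocks. The plan states no predictability figure to reproduce.

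*Observer who knows every past allocation and the block boundaries.* A block of two A and two B has 6 equally likely orders.

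- Position 1: correct guess 1/2; never certain.
- Position 2: guess the arm not yet used; correct 2/3; never certain.
- Position 3: the first two match in 2 of 6 orders, so it is certain with probability 1/3. Otherwise it is a coin toss. Correct: 1/3 + (2/3)(1/2) = 2/3.
- Position 4: always certain; correct 1.

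Certain: (0 + 0 + 1/3 + 1)/4 = 33.3%, and 84 × 1/3 = 28 assignments.
Correct guesses: (1/2 + 2/3 + 2/3 + 1)/4 = 70.8%, and 84 × 0.7083 = 59.5, against 50% (42) with no information.

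*Observer who uses only the running imbalance, not the boundaries.* The next assignment is certain only when the imbalance reaches 2. That happens at position 3 in one third of blocks: (1/3)/4 = 8.3%. Guessing the under-represented arm is still right 70.8% of the time.

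*Comparison: sizes 4, 6 and 8 chosen at random, boundaries hidden.* A simulation of 20,000 trials of 84 patients, with the observer using the running imbalance, gave 67.9% correct guesses and 0.16% (about 0.2%) certain assignments.

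| Design and observer | Certain | Correct guess |
|---|---|---|
| Fixed 4, boundaries known | 33.3% | 70.8% |
| Fixed 4, running imbalance only | 8.3% | 70.8% |
| Varied 4/6/8, running imbalance only | about 0.2% | about 68% |

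The like-for-like comparison is row 2 with row 3. Row 1 with row 3 changes both block size and knowledge of boundaries. That contrast is still relevant, because a fixed published size lets boundaries be counted from the first patient, whereas varied concealed sizes do not. The 0.2% counts only what the running imbalance reveals; someone holding the full ordered history could occasionally deduce a little more.

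**Could staff learn past allocations?** Recruitment from 1 September 2025 to 30 September 2026 is about 56 weeks. 84/56 = 1.5 patients per week, and 1.5 × 4 weeks of treatment gives about 6 under treatment at once if accrual is even. That is more than one block. Under Intervention, experimental patients have an extra session each morning and afternoon.

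**The case against.** On roles, the opposing case is that Randomization and blinding already sets out a sound chain, and the Exclusion criteria sentence is a loose summary that one wording change would align. That is fair as to remedy, and it makes this an inconsistency to reconcile. It does not remove the contradiction.

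A reader might infer that the primary outcome is scored by someone who knows the allocation. The documents do not support that: assessors are separate and blinded throughout, and data entry is blinded too.

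On predictability, the objection is stronger. The article does not say that the recruiting physician sees who practises Tai Chi, nor does it describe that physician as a treating therapist. Half of each day's Tai Chi is one-to-one with a therapist, and half is supervised by a caregiver. Randomization follows eligibility and consent, with opaque envelopes and a separate coordinator. The figures of 33.3% and 70.8% need someone to have followed every allocation in order. All of this stands: the leak is plausible but not documented, and the figures are a worst case. The envelopes hide the next assignment but do not prevent inference from earlier ones.

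It is also fair that varied blocks do little for simple guessing, and that adjustment for baseline FMA-UE could reduce bias acting through measured prognosis. It could not reach unmeasured prognosis.

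**Conclusion.** The role contradiction is certain on the text. Its reach is limited to data handling, disclosure of allocation and the truth of the blinding claim.

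The block-size weakness holds as a risk. If department staff learn past allocations, between 8.3% of assignments (running imbalance only) and 33.3%, about 28 of 84 (boundaries also known), are certain in advance, and 70.8% can be guessed correctly. This assumes one recruiting site with one list, so the four centres mentioned in Quality control must be reconciled with the single-centre description. It would go too far to say that upcoming allocations are predictable in general, that recruiters are known to see them, or that no analysis could reduce the resulting bias.

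Both points merit correction while recruitment is open, because the changes are small.

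**What to change.** 1. Amend the Exclusion criteria paragraph to match Randomization and blinding: the designated coordinator handles assignment and has no part in collecting or handling outcome data, and a different, blinded person collects the data.
2. From the next unused block, have the independent statistician issue a list with randomly varied block sizes (for example 4, 6 and 8). Withhold the sizes and the list from all site staff, and leave the sizes out of public text until recruitment closes.
3. Reconcile the single-centre description with the four centres in Quality control, and state which sites the list covers.

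The cost is one reassigned task, a new list for the remaining patients, and the amendment steps that Quality control already requires. Fixed blocks of 4 end exactly balanced at 84. With a largest block of 8, an incomplete last block could leave a difference of at most 8/2 = 4 patients, for example 44 against 40. The change protects only patients still to be randomized. Its gain is the loss of nearly all certain assignments, since simple guessing falls only from about 71% to about 68%.
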